## Abstract

**Background:**

Developing non-pharmacological interventions with strong potential to prevent or delay the onset of Alzheimer’s disease (AD) in high-risk populations is critical. Aerobic exercise and cognitive training are two promising interventions. Aerobic exercise increases aerobic fitness, which in turn improves brain structure and function, while cognitive training improves selective brain function intensively. Hence, combined aerobic exercise and cognitive training may have a synergistic effect on cognition by complementary strengthening of different neural functions. Few studies have tested the effects of such a combined intervention, and the findings have been discrepant, largely due to varying doses and formats of the interventions.

**Methods/design:**

The purpose of this single-blinded, 2 × 2 factorial phase II randomized controlled trial is to test the efficacy and synergistic effects of a 6-month combined cycling and speed of processing training intervention on cognition and relevant mechanisms (aerobic fitness, cortical thickness, and functional connectivity in the default mode network) in older adults with amnestic mild cognitive impairment. This trial will randomize 128 participants equally to four arms: cycling and speed of processing, cycling only, speed of processing only, or attention control for 6 months, and then follow them for another 12 months. Cognition and aerobic fitness will be assessed at baseline and at 3, 6, 12, and 18 months; cortical thickness and functional connectivity at baseline and at 6, 12, and 18 months; Alzheimer’s disease (AD) conversion at 6, 12, and 18 months. The specific aims are to (1) determine the efficacy and synergistic effects of the combined intervention on cognition over 6 months, (2) examine the underlying mechanisms of the combined intervention, and (3) calculate the long-term effect sizes of the combined intervention on cognition and AD conversion. The analysis will use intention-to-treat and linear mixed-effects modeling.

**Discussion:**

This trial will be among the first to test the synergistic effects on cognition and mechanisms (relevant to Alzheimer’s-associated neurodegeneration) of a uniquely conceptualized and rigorously designed aerobic exercise and cognitive training intervention in older adults with mild cognitive impairment. It will advance Alzheimer’s prevention research by providing precise effect-size estimates of the combined intervention.

**Trial registration:**

ClinicalTrials.gov, NCT03313895. Registered on 18 October 2017.

## Background

Preventing Alzheimer’s disease (AD) is the most important approach for tackling the AD epidemic. In 2018, AD afflicts 5.7 million Americans at a cost of $277 billion and up to 14 million Americans by 2050. In 2017, 16.1 million American family caregivers provided 18.4 billion hours of unpaid care valued at $232 billion [1]. However, no drugs can yet prevent, treat, or even slow down the progression of AD [2]. Mild cognitive impairment (MCI) is the prodromal stage of AD with well-defined diagnostic criteria and phenotype [3], representing a critical opportunity for AD prevention. MCI has an annual incidence rate of 51–77 per 1000 [3]. For amnestic MCI (aMCI), there is a cumulative 32% conversion rate to AD or other dementia [4]. Individuals with MCI are highly motivated to engage in interventions to prevent further cognitive decline [5, 3]. Currently, aerobic exercise and cognitive training are the two most promising non-pharmacological interventions for preventing conversion from MCI to AD [6].

Aerobic exercise refers to physical activity that uses large muscle groups to maintain continuous and rhythmic movements to improve aerobic fitness (the ability of the heart to deliver oxygen to working muscles), which is measured by peak oxygen consumption (VO_2peak_) [7]. Epidemiological evidence has consistently supported exercise’s link to reduced AD risk [8–12]. Randomized controlled trials (RCTs) have demonstrated that aerobic exercise such as cycling produced modest to moderate gains across cognitive domains in persons with intact cognition [13–16], MCI [17, 18], or dementia [15, 19]. The effect of aerobic exercise on cognition or AD risk may be explained by the relationship between aerobic fitness and brain integrity. High aerobic fitness has been associated with less brain atrophy [20–24] and stronger functional connectivity [25–28] across the brain in older adults with intact cognition or early AD.

Cognitive training involves repeated practice of a set of standard cognitive tasks targeting specific cognitive domains [29]. Targeting cognitive processes (e.g., attention) may produce more robust and broadly generalizable effects than targeting cognitive structures (e.g., delayed recall) [29–31]. Previous studies found that such process-based cognitive training generated a moderate to large improvement in selected cognitive domains in older adults with intact cognition or MCI. For example, attention training, such as speed of processing (SOP) training, has positive effects on sustained and divided attention [32], perfusion of the prefrontal cortex, and the functional connectivity between the occipitotemporal areas [33, 34] as well as within the default mode network (DMN) [35].

The preceding evidence indicates that aerobic exercise and cognitive training affect brain structure and function as well as cognition via distinct mechanisms. Combined Aerobic exercise and Cognitive Training (ACT) may build upon the strength of each intervention while concomitantly offsetting its relevant weakness to maximize the effects of these interventions for slowing the progression of AD, essentially due to their additive/synergistic neural effects. In other words, aerobic exercise that occurs in a cognitively challenging environment may produce greater cognitive and neural benefits than exercise alone [36–39]. Animal research indicates that aerobic exercise causes a large increase in new neurons, but at least half of them undergo apoptosis within weeks [40, 41]. Fortunately, these neurons can be rescued to become functional if trained with challenging cognitive tasks over time [36, 39, 41]. Aerobic fitness may also strengthen the neural plasticity obtained from cognitive training [40]. In humans, ACT intervention studies are few, with discrepant findings due to different intervention components, doses, and delivery formats [42–46]. Historically, ACT has been examined in two formats: concurrent (e.g., exergames, combining physical exercise with virtual reality training) vs. sequential (e.g., one after another). Whereas the exercise components can be comparable, the two formats differ considerably in the cognitive component (virtual reality such as scenery vs. cognitive training). Furthermore, the exact design of the sequential format lacks clarity. For example, a study using sequential design did not specify how the two components were delivered (e.g., on the same day or on different days; if on the same day, the amount of time lapse between the two components) [42]. A recent study of ACT failed to find a significant effect on gray matter in MCI, which may also be due to the lack of consideration of the intervention format [47]. Hence, there is a critical need to develop different delivery formats of ACT interventions that are maximally potential and implementable and investigate their effects and mechanisms of action. Such studies are best addressed by phase II trials which are also considered stage II trials according to the National Institutes of Health (NIH) Stage model [48].

### Study aims

The purpose of this phase II RCT is to test the efficacy and additive/synergistic effects of an ACT intervention (cycling and SOP training), by comparing it to cycling and SOP training alone and an attention control (stretching and mental leisure activities), on cognition and relevant mechanisms (aerobic fitness, AD signature cortical thickness, and DMN) in older adults with amnestic MCI (aMCI). Here we choose AD signature cortical thickness [49] and DMN [50] since they are common neural markers detected early in the progression of AD. The study is funded by the NIH’s National Institute on Aging (R01AG055469-01A1, 9/15/2017–5/31/2022). The specific aims and hypotheses of the study are described as follows:Aim I. Determine the efficacy and additive/synergistic effects of ACT on cognition over 6 months

*Hypothesis 1*. ACT will have the greatest effects on executive function and episodic memory compared with other groups.Aim II. Examine the underlying mechanisms of ACT over 6 months

*Hypothesis 2a*. ACT will have the greatest effects on AD signature cortical thickness, functional connectivity in the DMN, and aerobic fitness compared with other groups.

*Hypothesis 2b*. Changes in the mechanistic measures are related to cognitive changes.

*Hypothesis 2c*. Changes in AD signature cortical thickness and DMN mediate aerobic fitness effects on cognition.Aim III (exploratory). Calculate the long-term effect sizes of ACT on cognition and clinical AD conversion to inform future phase III RCTs

## Methods

### Design

This RCT will use a single-blind, multi-site, 2 × 2 factorial design, guided by the Consolidated Standards of Reporting Trials (CONSORT) [51] and the Standard Protocol Items: Recommendations for Interventional Trials (SPIRIT) checklist [52]. We will randomize 128 older adults with aMCI equally to one of four arms for 6 months (*n* = 32 in each group): ACT; cycling only; SOP training only; or attention control. Based on our previous studies (Fig. 1) [35, 53, 54], we anticipate screening approximately 384 individuals in person to enroll 128 participants. Participants will then be followed for another 12 months (*n* = 96 at 6 months with 25% attrition and *n* = 84 at 18 months with 35% attrition). We will stratify randomization by site (University of Minnesota [UMN] and University of Rochester [UR]) and age (< 75 and ≥ 75 years), using random permuted blocks of 4 and 8 participants. Cognition and aerobic fitness will be assessed at baseline and at 3, 6, 12, and 18 months; AD signature cortical thickness and DMN at baseline and at 6, 12, and 18 months; AD conversion at 6, 12, and 18 months.

**Fig. 1 Fig1:**
[figure not shown]
Schedule of enrollment, interventions, and assessments

### Setting

Screening and non-imaging data collections will occur in a private room at the Clinical and Translational Science Institute and Laboratory of Clinical Physiology at UMN and the CogT Lab at UR. Imaging will occur at the Center for Magnetic Resonance Research at the UMN and the Rochester Center for Brain Imaging at the UR. Both centers have participated in multi-site imaging studies with harmonized MRI protocols previously. The interventions will occur at a local YMCA gym or senior center close to the participant’s residence.

### Study population

#### Recruitment

We plan to enroll 128 participants within 3.5 years (4–5 participants a month) with a proactive recruitment plan, including clinic referrals, recruitment material distributions in the communities, exhibits at relevant conferences, and media such as newspaper advertisements. We will emphasize minority recruitment by educating providers serving minorities, collaborating with community gatekeepers, and hiring specialists for minority recruitment. In the event that recruitment goals are not being met, we will consider zip code mass mailing, initiate recruitment from other health systems outside the two universities, and reach out to suburban and rural neighborhoods.

#### Eligibility and screening

Potential participants who respond to our recruitment strategies and initiate contact with us will be carefully screened for eligibility and safety using a three-step procedure, including a phone interview, an in-person interview, and a symptom-limited peak cycle-ergometer test and magnetic resonance imaging (MRI) scan to ensure they meet our eligibility criteria (Table 1).Phone interview: The staff will get the respondent’s verbal consent for participating in the phone and in-person screenings. The staff will elicit self-reported health history and exercise/MRI risk. Potential participants who pass the phone screen will be scheduled for an in-person interview.In-person interview: Informed consent and Health Insurance Portability and Accountability Act (HIPAA) authorization will be obtained. The study staff will corroborate phone screen data, administer instruments to assess clinical diagnosis of aMCI, conduct a focused physical assessment, and complete the MRI safety checklist. During informed consent, individuals will be informed about the study procedure, data collection, time commitment, the voluntary nature of study participation, risks, benefits, compensations, and contact within and outside the study team for human subjects. Letters will be sent to the potential participant’s medical providers to obtain medical clearance for exercise and MRI. Medical clearance from a cardiologist will also be obtained if a participant has a significant cardiac history and has a cardiologist. The investigator team will make safety decisions for those who do not have a cardiologist.Symptom-limited peak cycle-ergometer test and MRI: Upon receiving safety clearance for exercise, potential participants will undergo a symptom-limited peak cycle-ergometer test to further rule out unknown cardiac ischemia and serious arrhythmia and to obtain peak heart rate (HR) for calculating HR reserve. Resting seated and standing HR, blood pressure, and electrocardiograms will be evaluated to ensure safety prior to performing the test. HR and rhythm will be continuously monitored during exercise, and blood pressure will be monitored every 3 min during the test. The test will be stopped if any of the American College of Sports Medicine (ACSM) indications for absolute or relative test termination are met. The test will be conducted in the exercise labs by trained lab technicians, interventionists, or their designees. The supervising clinicians will determine if the criteria for ending the test are met, or if the test needs to be terminated, and whether participants can proceed towards enrollment. Participants who pass the symptom-limited peak cycle-ergometer test and have no contraindications for the MRI will undergo a 30-min scan to see if they any have brain abnormalities that are clinically significant to warrant a follow-up medical evaluation and/or would interfere with a research definition of MCI such as normal pressure hydrocephalus, brain tumor, subdural hematoma, significant post-traumatic encephalomalacia, or one or more large hemispheric infarctions. Participants with clinically significant brain abnormalities will be referred to their primary care providers for medical follow-up and will be considered for study participation only if the providers medically clear them. Those who have no brain abnormality and those who have clinically significant brain abnormalities but have been medically cleared will be formally enrolled in the study upon completing baseline data collection and randomized after baseline data collection.

**Table 1 Tab1:** Eligibility criteria

Inclusion criteria	Exclusion criteria
a) A clinical, *consensus* diagnosis of aMCI (mono-domain or multi-domain): ◦ 18 ≤ Montreal Cognitive Assessment score ≤ 26 (education-corrected) ◦ Memory deficits: at least 1 standard deviation below age- and/or education-corrected population norms on Rey Auditory Verbal Learning Test ◦ Preserved activity of daily living: Activities of Daily Living-Prevention Instrument score < 30 ◦ Absence of dementia ◦ A consensus clinical diagnosis of MCI (using 2011 Alzheimer’s association-NIA criteria) by the investigators b) Community-dwelling, e.g., homes and assisted living c) Age 65 years and older d) English-speaking e) Adequate visual acuity for testing f) Verified exercise safety g) Stable on drugs affecting cognition > 3 months, if on these drugs h) Verfied MRI scan safety i) Capacity to consent	a) Geriatric Depression Scale score > 5, with contextual evidence suggesting unstable major depression or psychiatric disorders such as taking antidepressant less than 3 months b) Resting HR ≤ 50 due to arrhythmia or ≥ 100 beats/min c) Neurologic, psychiatric, or substance abuse disorders in past 5 years that are the main contributor to MCI d) ACSM contraindications to exercise e) New, unevaluated symptoms or diseases f) Current enrollment in another intervention study g) Abnormal MRI findings

*ACSM* American College of Sports Medicine, *HR* heart rate, *MCI* mild cognitive impairment, *MRI* magnetic resonance imaging, *NIA* National Institute on Aging

#### Sample size and power

We determined the sample size based on anticipated effect sizes, attrition, and the literature. For Aim I, a sample size of 128 at 25% attrition will give us a final analytical sample of 96 at 6 months. Our previous study of SOP training had a partial η^2^ = 0.28 for working memory [35], while cycling had a value *r*^2^ = 0.35 for slowing the worsening of ADAS-Cog (the Alzheimer’s Disease Assessment Scale-Cognition, a global cognition measure [55]. Here, with an estimated, conservative effect size for the change in cognition for ACT (compared with attention control) of 0.25, we will have 80% power to detect group differences in both episodic memory and executive function. For Aim II, our previous study of SOP training had a partial η^2^ = 0.62 for mechanistic effect [35]. Using a type I error rate of 0.05, up to three repeated measures (0, 3, and 6 months), and a correlation between measures of 0.5, we only need 58 participants to have 86% power to detect a significant difference in the change in AD signature cortical thickness and DMN with an effect size (partial η^2^) of 0.08. Aim III is exploratory and not powered. A 35% attrition at 18 months will result in a final analytical sample of 84 to calculate ACT’s long-term effect sizes to inform future RCTs.

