#### Aim II. Examine the underlying mechanisms of ACT over 6 months

Aim II involves the following hypotheses 2a–2c:

*Hypothesis 2a*. Linear mixed-effects models similar to the ones developed in H1 will be fit for AD signature cortical thickness, functional connectivity in the DMN, and aerobic fitness. We will obtain the model-based estimates of the change in these mechanistic measures by randomized groups to determine which group had the largest change, and we will conduct a composite hypothesis test to assess if the changes in aerobic fitness at 3 and 6 months and in AD signature cortical thickness and DMN at 6 months differ significantly by group.

*Hypothesis 2b*. We will consider the same linear mixed-effects models as in H1 but will include changes in AD signature cortical thickness, functional connectivity in the DMN, and aerobic fitness at the corresponding time point in the models. Because of likely collinearity in these measures, separate models will be fit for each measure.

*Hypothesis 2c*. We will fit a longitudinal mixed-effects model (similar to H1) for the change in cognition, which will include both the change in aerobic fitness and the mediator’s changes in AD signature cortical thickness and functional connectivity, and longitudinal mixed-effects models for the changes in AD signature cortical thickness and functional connectivity that include aerobic fitness as a predictor. The estimated controlled direct effect and natural indirect effect can then be easily derived from the estimated coefficients of these models.

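### The Aim II imaging power assumes a 3-month scan that is not scheduled, and 58 participants with 86% power cannot be obtained from the stated inputs for the planned four-arm test

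*Protocol article*

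**What the plan says.** The Sample size and power section gives the Aim II imaging calculation in one sentence. It begins with "Using a type I error rate of 0.05" and continues with "up to three repeated measures (0, 3, and 6 months), and a correlation between measures of 0.5, we only need 58 participants". The result is 86% power, at a partial eta-squared of 0.08, for a difference in the change in cortical thickness and DMN connectivity. The sentence names no other outcome. It does not state the test, the number of groups or how partial eta-squared is defined.

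The Design section schedules "AD signature cortical thickness and DMN at baseline and at 6, 12, and 18 months". The Abstract, the Primary outcomes section and Table 2 agree, and in Table 2 month 3 is blank for both MRI rows. The Data collection section lists visits differently but also has no 3-month MRI. Under Hypothesis 2a, aerobic fitness is tested at 3 and 6 months, while the imaging test asks whether changes "in AD signature cortical thickness and DMN at 6 months differ significantly by group".

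The trial randomizes 128 participants equally to four arms and expects 96 to be analysed at 6 months.

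**The concern.** The power sentence describes three measurements of outcomes that are measured twice in the Aim II period. The outcome that does have three, aerobic fitness, is not in the sentence. The wording that allows up to three measures does not resolve this, because neither named outcome ever has three by month 6.

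The pair 58 and 86% also looks wrong in itself, since the usual power formulas for a four-arm test of change give quite different values.

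The sentence is the only support for the claim that the imaging outcomes need far fewer participants than the trial will have. If that margin is not real, a null imaging result could be misread as evidence against the proposed mechanism.

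**Working it through.** **Inputs.** From the article: alpha 0.05; partial eta-squared 0.08; correlation ρ = 0.5; k = 4 arms; N = 58 (stated) or 96 (expected at 6 months); m = 3 measures (as stated) or m = 2 (as scheduled).

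f² = 0.08 / (1 − 0.08) = 0.0870.

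**Test.** This is the group-by-time F test, the repeated-measures ANOVA counterpart of the planned group comparison of change. Degrees of freedom are df1 = (k − 1)(m − 1) and df2 = (N − k)(m − 1). Power is the upper tail of the noncentral F distribution beyond the 5% critical value. The article does not say how 0.08 enters the noncentrality λ, so three conventions are shown:

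- A: λ = f² × N × m / (1 − ρ), the only one that uses the stated correlation.
- B: λ = f² × N × (m − 1).
- C: λ = f² × (N − k) × (m − 1), where partial eta-squared is the F-test ratio and already reflects the correlation.

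B and C are close variants of the F-ratio reading.

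**Step 1: the plan's own figure (N = 58, m = 3; df 6 and 108).**

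- A: λ = 0.0870 × 58 × 3 / 0.5 = 30.3; power 99.1%
- B: λ = 0.0870 × 58 × 2 = 10.1; power 61.8%
- C: λ = 0.0870 × 54 × 2 = 9.4; power 58.2%

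None is near 86%. The N that gives 86% is 34 (A), 94 (B) or 97 (C), not 58. A two-group version with three measures gives 99.9%, 80.8% or 79.3%, which also misses.

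**Step 2: two scans, N = 58 (df 3 and 54).**

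- A: λ = 0.0870 × 58 × 2 / 0.5 = 20.2; power 96.6%
- B: λ = 0.0870 × 58 = 5.0; power 41.6%
- C: λ = 0.0870 × 54 = 4.7; power 38.9%

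**Step 3: two scans, N = 96 (df 3 and 92).**

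- A: λ = 0.0870 × 96 × 2 / 0.5 = 33.4; power 99.9%
- B: λ = 0.0870 × 96 = 8.3; power 65.4%
- C: λ = 0.0870 × 92 = 8.0; power 63.3%

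**Step 4: effect detectable with 80% power (N = 96, two scans).** With df 3 and 92, 80% power needs λ of about 11.4.

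- C: f² = 11.4 / 92 = 0.124, so partial eta-squared = 0.124 / 1.124 = 0.11. B gives about the same (11.4 / 96 = 0.119; 0.119 / 1.119 = 0.106).
- A: f² = 11.4 × 0.5 / (96 × 2) = 0.030, so partial eta-squared is about 0.03.

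**Step 5: is there any route to 86% at 58?** A single-degree-of-freedom contrast on the F-ratio reading, with three measures and 108 error df, has λ = 0.0870 × 108 = 9.4 and power 85.9%. With two scans (54 error df, λ = 4.7) the same contrast gives 56.7%. A one-sided, two-group, time-averaged comparison gives 85.8% with three measures and 82.0% with two. The article states neither test, and neither is the planned four-arm comparison of change.

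**The case against.** The strongest reply is that the article is condensed and names no test, so failure under one chosen test does not prove the figure wrong. The single-df contrast does give 85.9%, and a hypothesis that the combined arm does best makes a focused contrast plausible. This stands in part: the fair statement is that 58/86% does not follow from the stated inputs for the planned composite test, not that no calculation could produce it. The schedule point is unaffected, because that contrast drops to 56.7% with two scans.

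A second reply is that the direction of the error is unknown. This stands. The stated 0.5 correlation enters only convention A, and there 58 is more than enough even with two scans. A reader might infer from the 39% or 63% that the imaging aims are underpowered. The documents do not support that conclusion, because they do not select the F-ratio reading. They do not exclude it either.

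A third reply is that 58 sets neither the 128 randomized nor the 96 expected. That is correct, and it limits the consequence to what is claimed about imaging power.

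A reader might also infer that Hypotheses 2b and 2c fail because no imaging change exists at month 3, given that 2b uses changes in imaging, "functional connectivity in the DMN, and aerobic fitness at the corresponding time point in the models". The text does not support this. Hypothesis 2a already confines imaging to 6 months, and 2b fits a separate model for each measure, so the imaging models naturally use month 6 and the fitness models keep both visits. At most this needs a clarifying phrase.

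**Conclusion.** The schedule mismatch is certain from the text: the power sentence counts a 3-month scan for two primary outcomes that have none. It is also established that 58 participants and 86% power cannot be obtained from the stated inputs for the planned four-arm test of change under any of the three conventions examined.

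The size and sign of the error are not established. With the two planned scans, power at the expected 96 is about 63–65% on the F-ratio reading and over 99% on the correlation-based reading. These figures assume equal arms, an omnibus group-by-time F test at 0.05 and complete data on the 96. A statement that could mean 39% or 97% at its own sample size does not support the claim of ample imaging power.

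**What to change.** Recompute the Aim II imaging power for the planned four-arm test with two scans (0 and 6 months). State the test and the definition of partial eta-squared. Replace 58/86% with the resulting power at 96 analysed participants, or with the effect detectable at 80% power (about 0.11 if the F-ratio definition was meant, about 0.03 if the correlation-based one was). If a focused contrast was intended, say so and recompute it with two scans. Optionally, add to Hypotheses 2b and 2c that the imaging models use the month-6 change.

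The cost is one recalculation and the rewording of one sentence, plus the optional clarification. No new data are needed, and neither the planned tests nor the sample size need change on this account alone.
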